#### Secondary Outcomes

Secondary outcomes will include the difference in change in albuminuria status; change in eGFR, systolic blood pressure, and low-density lipoprotein cholesterol level; change in the proportion of patients with HbA_1c_<7%, and patients with systolic blood pressure<140 mm Hg; measured at randomization and 12 months from randomization, between the intervention and control clusters.

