## Introduction

### Background

South-East Asian countries (including Thailand) have been experiencing a steady rise in the burden of noncommunicable diseases (NCDs). The Global Burden of Disease Study 2015 reported diabetes and chronic kidney diseases (CKD) as Thailand's third and fifth leading causes of death [1]. According to the 5th Thai National Health Examination survey conducted in 2014 [2], Thailand has 4.63 million adults with diabetes (9.9% of the adult population), which is expected to grow to 5.2 million by 2035. In addition, 7 million adults in Thailand have prediabetes due to increasing childhood and adolescent obesity and is estimated that 25%-48% of people with diabetes will develop CKD [3]. According to the Microalbuminuria Prevalence Study survey in 2002 [4] across 10 Asian countries, it was found that 45% of the population in Thailand with diabetes had microalbuminaria and 15% had macroalbuminaria. Both conditions increase the risk for the development and progression of CKD, which will eventually lead to the need for dialysis or a kidney transplant. According to data from the Thai Renal Registry, diabetes was responsible for 34.6% cases of kidney failure in 2007 [5], increasing to 41.5% in 2020 [6]. Suboptimal treatment of diabetes leads to other macro- and microvascular complication such as cardiovascular disease, neuropathy, and retinopathy, all of which are associated with the use of more resources [7] and have grave economic and health impact.

The risk of suboptimal care and poor outcomes is worse among the socioeconomically disadvantaged. According to the World Bank reports, about 4.9 million people in Thailand live below poverty lines, with catastrophic health care cost being one of the factors contributing to relapse into poverty [8]. However, the launch of the universal health coverage program in Thailand that provided a comprehensive benefits package and zero copayment for health services was followed by a progressive decrease in the number of households (6% in 1996 to 2% in 2015) that experienced financial catastrophic events (defined as out-of-pocket payment for health exceeding 10% of household total consumption expenditure) due to health care [9].

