### Statistical Considerations

Randomization of 51 SDHOs with an average cluster size of 40 individuals with diabetes at baseline will provide 90% power (2α=0.05) to detect an absolute mean HbA_1c_ difference of 0.5%. A change of 0.5% in HbA_1c_ is considered clinically meaningful [26]. Intracluster correlation coefficients of 0.05 for HbA_1c_ are assumed. By assuming a 10% dropout rate in our study, the sample size calculation indicated that a total of 1540 participants will be required to be recruited in both arms, with 770 in each group (Figure 2).

The analysis of change in HbA_1c_ between baseline and the end of study (primary end point) will be performed using a linear mixed model including treatment arm and baseline HbA_1c_ as fixed effects as well as SDHO as a random effect to account for clustering of individuals by village. In case of baseline imbalances between the 2 arms at the cluster or individual level, unbalanced characteristics will be added to the models as a sensitivity analysis. The same approach will be applied for continuous secondary end points.

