### Data Collection and Management

Data collection will commence at baseline (0 months; randomization) and will be conducted quarterly at 3, 6, 9, and 12 months after randomization by community nurses. All data will be captured on tablet devices using the SMARThealth app adapted for the clinical research forms (CRFs). The CRFs collect information on anthropometric measurements, medical history, and current medication for hypertension, diabetes, and hyperlipidemia, in addition to laboratory test results. These CRFs will be completed at months 0, 3, 6, 9, and 12. The primary outcome variable (HbA_1c_) and other laboratory tests will only be recorded at months 0, 6, and 12. Data will be deidentified, saved, and stored in a secure server located in Bangkok, Thailand. Published, validated questionnaires are used in the CRFs and tested using the SMARThealth platform before data collection. About 10% of all CRFs will be checked for accuracy against source data by the project team.

SMARThealth platform will be used for digitally collecting all baseline and outcome data. Data access will be restricted to delegated study staff and will require multifactor identification with a digital log kept of all logins. The project manager and data managers will be responsible for data quality. The project manager will ensure quality by interacting periodically with community nurses and checking for completeness of data, and data validation.

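### Albuminuria is listed only as a change in status; if a quantitative ratio is recorded, comparing categories loses more than half of its information

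*Protocol article*

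**What the plan says.** The Secondary Outcomes section of the Protocol article names "the difference in change in albuminuria status", and the Abstract uses the same term, status. The time points for the whole list are given as "measured at randomization and 12 months from randomization, between the intervention and control clusters".

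The same sentence lists eGFR, systolic blood pressure and LDL cholesterol as changes in the measure itself. Where it uses a threshold (HbA1c below 7%, systolic pressure below 140 mm Hg), the continuous version is also an outcome: HbA1c as the primary, systolic pressure in the same list. Albuminuria has no such partner.

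Statistical Considerations specifies a linear mixed model for HbA1c, with arm and baseline value as fixed effects and SDHO as a random effect. It then adds: "The same approach will be applied for continuous secondary end points". No other model for secondary outcomes appears in the article.

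The article does not give the assay, the cut-offs, or the number of urine samples per visit.

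**The concern.** A category throws away movement inside its limits. A patient whose ratio halves without crossing a cut-off counts as unchanged, while a patient close to a cut-off can change category through sample-to-sample variation alone. Patients in the lowest category cannot improve and those in the highest cannot worsen. With the mix quoted in the Background ("45% of the population in Thailand with diabetes had microalbuminaria and 15% had macroalbuminaria", which leaves 40% normal), 40% + 15% = 55% of patients could move in one direction only.

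The trial's hypothesis links better glucose control to fewer renal complications, and albuminuria and eGFR are the only kidney outcomes listed. A real effect on albuminuria could be diluted, and a null result on status would then say little. The model that would use the full value is already in the article but, as worded, does not reach this outcome.

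**Working it through.** **The plan's own figure.** There is none for albuminuria. The sample size of 1540 is for HbA1c and does not bear on this point.

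**Inputs.** From the document: the 45% micro and 15% macro prevalences (Background; an older survey, not this trial's patients). All the rest are my assumptions:
- a second, milder mix of 70/25/5%, because entry requires eGFR above 60 and excludes nephrotic syndrome;
- cut-offs of 30 and 300 mg/g;
- ln(ratio) normally distributed, with one sample per time point;
- within-person SD s_w of ln(ratio) of 0.30, 0.45 or 0.60;
- SD of true 12-month change in ln(ratio) of 0.5;
- treatment effect of a 20% reduction, ln(0.80) = −0.223.

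**Step 1: distribution of ln(ratio).** SD s = [ln 300 − ln 30] / (z_upper − z_lower); mean = ln 30 − z_lower × s.
- 40/45/15%: s = 2.303 / (1.036 + 0.253) = 1.785; mean = 3.401 + 0.253 × 1.785 = 3.853.
- 70/25/5%: s = 2.303 / (1.645 − 0.524) = 2.055; mean = 3.401 − 0.524 × 2.055 = 2.324.

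**Step 2: noise alone.** Draw two samples per patient around an unchanged true value and count those whose category differs.

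**Step 3: relative efficiency.** For each analysis, take (mean treatment shift)² / (variance of the analysed quantity), then divide the status value by the log-ratio value. Status is scored 0, 1, 2 and analysed either as a plain change or adjusted for baseline category. The variance of baseline-adjusted ln(ratio) is s² + 0.5² − (s² − s_w²)² / s².

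Worked case, 40/45/15% mix with s_w = 0.45:
- Log ratio: variance = 3.186 + 0.25 − (2.984)² / 3.186 = 0.642; 0.223² / 0.642 = 0.0775.
- Status change (simulated): mean shift −0.0745, variance 0.2233; 0.0745² / 0.2233 = 0.0249. Relative efficiency = 0.0249 / 0.0775 = 0.32.
- Status adjusted for baseline category: variance 0.2012; 0.0745² / 0.2012 = 0.0276. Relative efficiency = 0.0276 / 0.0775 = 0.36.

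All cases (2,000,000 simulated patients each):

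| Mix | s_w | Change status from noise alone | Efficiency, plain status change | Efficiency, status adjusted for baseline category |
|---|---|---|---|---|
| 40/45/15% | 0.30 | 11.8% | 26.5% | 28.7% |
| 40/45/15% | 0.45 | 17.7% | 32.1% | 35.6% |
| 40/45/15% | 0.60 | 23.6% | 38.2% | 43.7% |
| 70/25/5% | 0.30 | 7.4% | 16.5% | 17.7% |
| 70/25/5% | 0.45 | 11.2% | 20.0% | 22.0% |
| 70/25/5% | 0.60 | 14.9% | 23.7% | 26.8% |

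The ranges are about 7% to 24% for noise and about 16% to 44% for efficiency. The loss remains when status is also adjusted for baseline, so it comes from categorising and not only from missing adjustment.

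**Step 4: wider assumptions.** With a within-person CV of 0.3 to 0.7 and a true-change SD of 0 to 0.6, noise alone moves 7% to 25% of patients, and the baseline-adjusted category analysis keeps 11% to 46%. Every scenario is below half. Clustering was not simulated; the ratios carry over if both analyses have a similar design effect.

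**The case against.** The strongest reply is that the article hardly specifies this outcome. The list is introduced as what the secondary outcomes will include. Definition, assay and model may sit in a full protocol or SAP that is not shown, and a condensed article may properly leave them there. That stands against any claim that something is missing. It does not remove the point, because the article does fix the scale (status) and the time points (0 and 12 months), and it limits its model to continuous end points.

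Second, a quantitative value is not shown to exist. The platform draws on laboratory records already available at the SDHO, and the word status fits dipstick reporting. In that case no measured value is discarded. This stands in full, and the point is conditional on it.

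Third, apart from the Background prevalences every numerical input is assumed, and replicate samples per visit would reduce the noise. This also stands. It affects the size of the loss and not its direction.

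A reader might also infer that month 6 offers a remedy, since "other laboratory tests will only be recorded at months 0, 6, and 12", and might count a status change only if months 6 and 12 agree. The article does not name urine albumin among those tests, so a month-6 sample cannot be assumed. The rule would not help in any case. With the 40/45/15% mix and s_w of 0.30/0.45/0.60, its relative efficiency is 27/32/37% if the full effect is present by month 6, against 27/32/38% for plain status change. It falls to 14/17/20% if half the effect is present by then.

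**Conclusion.** The point holds conditionally. As listed, albuminuria is an outcome only as a change in status between randomization and 12 months and so lies outside the stated model for continuous secondary end points. If a quantitative ratio is recorded, comparing categories loses more than half of the information under every assumption tried: status keeps about 16% to 44% of the efficiency of baseline-adjusted log ratio, and about 7% to 24% of patients change status from noise alone. These figures rest on the assumed cut-offs, variability, effect size and category mixes given above.

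Stronger readings are tempting but not supported. The article does not say that status is the only analysis that will be done, that each visit yields a single sample, or that a measured value is being thrown away. Nor does it support calling albuminuria the renal marker most likely to respond within 12 months.

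The stakes are modest. The noise is expected to fall equally on both arms, so it dilutes one secondary outcome and does not touch the HbA1c analysis.

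**What to change.** Where the laboratory reports a quantitative albumin-creatinine ratio, add log(ratio) at month 12 to the secondary outcomes. Analyse it with the model in Statistical Considerations (arm and baseline log ratio as fixed effects, SDHO as a random effect) and report it as a ratio of geometric means. Keep the 12-month change in status as listed. Write this down before outcome data are examined by arm.

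The cost is one more secondary analysis and a summary less familiar to clinicians than a category, which is a reason to keep status beside it. It relies only on the month 0 and month 12 values that the listed outcome already needs. If only dipstick results exist, nothing needs to change.

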### Timeline

SDHOs will be recruited and randomized before individual participant recruitment commences. After randomization, community nurses in the intervention clusters will receive the training program (as described earlier). Eligible patients with diabetes registered within the SDHOs will be invited by the community nurses to participate in this study. After obtaining written informed consent, demographic and additional data, baseline parameters will be collected using previously validated, structured questionnaires. At the end of the study (12 months), data and biological samples will again be collected at the laboratory in SDHOs by trained laboratory technicians, along with completing the endline questionnaires by community nurses to allow analyses for all outcomes.

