##### Workflow Integration

Through the inputs from the health service assessment and ongoing discussions with nurses from SDHOs and doctors at health facilities, the SMARThealth platform was adapted to suit the existing workflow of the health offices. For example, the paper registration forms were digitized and integrated with the platform, the existing printers at the SDHOs are used to print treatment advice and referral cards, available laboratory records at SDHO are used for input into the platform, and mobile communication of doctors and nurses are retained through use of this platform.

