### Informed Consent

Consent will be obtained based on a professional-cluster design approach proposed by Hemming and Eldridge [25]. Consent will be collected at three levels: (1) at the cluster level —verbal approval from each SDHO to participate in the trial; (2) from the health workers—verbal approval from nurses and doctors to participate in the study and provide information during and after the study; and (3) from individual participants—consent from patients with diabetes interested in participating in the study for data collection during the study.

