### Intervention Group

SDHOs randomized to the intervention group will receive the SMARThealth Diabetes program described earlier.

First, a workforce restructuring and training program to increase the involvement of community nurses in routine aspects of diabetes and kidney disease care. Using the module developed in objective 1, training will be provided to community nurses to promote awareness of lifestyle determinants, use of the CDSS to record risk factor information from the laboratory records available at the health center, guidance in the interpretation of the CDSS output, and processes to refer high-risk individuals to the district hospitals and training to monitor and promote adherence to prescribed medications. The training will be imparted for 2 days. After training and certification, community nurses will each be provided with a 7-inch tablet preloaded with the SMARThealth software. Second, the Thai CDSS will incorporate components related to referral, follow-up, and personalized recommendations about blood glucose control, BP lowering, pharmacotherapy including ACE inhibition, statin, and eye and foot care. Third, continuous performance monitoring. The performance of community health nurses will be monitored using standard, automated reports generated in real time and based on certain key performance indicators (eg, the proportion of individuals with diabetes on recommended combination treatment). These reports will be provided to health administrators in each district.

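### The Timeline puts intervention-nurse training before baseline, while other sections date baseline to randomization; as written, the baseline HbA1c in the primary model can be post-training in one arm only

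*Protocol article*

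**What the plan says.** The Timeline section gives an order of events. First, "SDHOs will be recruited and randomized before individual participant recruitment commences". Next, "After randomization, community nurses in the intervention clusters will receive the training program (as described earlier". Then, "Eligible patients with diabetes registered within the SDHOs will be invited by the community nurses to participate in this study". Last, "After obtaining written informed consent, demographic and additional data, baseline parameters will be collected using previously validated, structured questionnaires". For month 12 it says that "data and biological samples will again be collected at the laboratory in SDHOs by trained laboratory technicians"; the word again implies that the baseline samples were also drawn within the study.

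Two other sections fit this order. Intervention Group says: "After training and certification, community nurses will each be provided with a 7-inch tablet preloaded with the SMARThealth software". Data Collection and Management has all data, month 0 included, captured on tablets in the SMARThealth app.

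Primary Outcome, Secondary Outcomes, and Data Collection and Management date the baseline measurement differently: they place it at randomization.

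Statistical Considerations fits a linear mixed model for change in HbA1c, with arm and baseline HbA1c as fixed effects and SDHO as a random effect. Under Control Group, control SDHOs receive neither the training nor the decision support.

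**The concern.** The intervention is aimed at the SDHO team, not at the individual who consents. Informed Consent describes the patient's agreement as "consent from patients with diabetes interested in participating in the study for data collection during the study", so on the text it does not switch the intervention on. Eligible patients include known cases already treated by the SDHO's community nurse. Such a patient could be seen by a trained nurse before giving a baseline sample. Training covers lifestyle, referral and adherence, so care could change even before the app is used for that patient.

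The baseline covariate would then carry part of the treatment effect in the intervention arm only, and adjusting for it removes that part. The estimate would be too small, and the baseline table would show partly treated values in one arm. The secondary outcomes measured against the same baseline (eGFR, systolic pressure, LDL cholesterol, albuminuria) would be exposed in the same way. The planned sensitivity analysis, which adds unbalanced characteristics to the model, would not help, since it could adjust away imbalances that early intervention had produced.

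This differs from the question of who is recruited after allocation is known: it would arise even with identical patients in both arms.

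**Working it through.** **Sequence.** The two accounts of baseline side by side:

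| Source | Where baseline falls |
|---|---|
| Timeline | After SDHO randomization, nurse training, invitation and consent, in that narrated order |
| Intervention Group with Data Collection and Management | Tablet issued after training and certification; all data captured on tablets |
| Primary Outcome, Secondary Outcomes, Data Collection and Management | At randomization |

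Patients are recruited after their SDHO is randomized, so a study sample taken after consent cannot coincide with randomization. The first two rows agree with each other; the third cannot be met as the Timeline stands.

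**Effect on the estimate.** Let Δ be the true 12-month difference, b the average HbA1c reduction already present at baseline in the intervention arm, and β the slope of 12-month HbA1c on baseline. Modelling change with baseline as a covariate gives the same arm coefficient as modelling the 12-month value with that covariate. An unadjusted change score corresponds to β = 1. Then

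estimate = Δ − β × b.

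**Inputs.** Δ = 0.5 is the difference the trial is powered for. The rest is assumed: β = 0.6, an effect that builds linearly over 12 months from training and then holds, and every patient exposed from the training date. With a gap of d months, b = 0.5 × d/12.

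| d (assumed) | b | Adjusted: 0.5 − 0.6b | Change score: 0.5 − b |
|---|---|---|---|
| 1 month | 0.042 | 0.475 | 0.458 |
| 3 months | 0.125 | 0.425 | 0.375 |

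The adjusted estimate loses 0.025/0.5 = 5% and 0.075/0.5 = 15%.

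**Share exposed.** If only a share p of patients meets a trained nurse before baseline, average b is p times the value above. With p = 0.5 and d = 3, b = 0.0625 and the adjusted estimate is 0.5 − 0.6 × 0.0625 = 0.4625. With p = 0 there is no loss.

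**Power, as a guide only.** The stated sample size cannot be reproduced, because no standard deviation is given. Solving for one: 1540 less 10% is 1386, or 693 per arm and 1386/51 = 27.18 per SDHO. The design effect is 1 + 26.18 × 0.05 = 2.309, leaving 693/2.309 = 300.2 effective patients per arm. Then SD = 0.5 × √(300.2/2)/(1.960 + 1.282) = 1.89 for 90% power. With that SD and β = 0.6, b = 0.05 gives an estimate of 0.47 and 86% power; b = 0.10 gives 0.44 and 81%.

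**The case against.** The best counter-argument is that exposure before baseline may be rare. According to the section on deploying the algorithms, the tool's output depends on patient data entered into it, and the SMARThealth section describes its medication support as given at follow-up. The platform also collects the baseline data, so the baseline visit may be a patient's first contact with it. Contamination then needs a separate encounter with a trained nurse beforehand, and nothing shows how often that happened. This stands, and it is why no size can be claimed.

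A second argument is that baseline is labelled as randomization, which read literally precedes training. The label suggests that a pre-intervention baseline was intended, but the Timeline does not secure one.

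A third is that go-live rules often sit in the full protocol, and the two design figures are not shown. That is fair: the lack of such a rule in an article would not by itself be a finding. The point rests on the order that the article states and on its conflict with the stated date of baseline.

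A reader might infer more than the text supports:

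- That training was complete before every baseline sample. The order is narrated, but no sentence says this.
- That most participants were known cases. Inclusion Criteria admits known and screen-detected cases without proportions.
- That the gap lasted many months, because data collection began in November 2022 and 1599 enrolments are reported as of May 2024. Those dates do not bound the interval between training and baseline in any SDHO.

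**Conclusion.** The point holds as a conflict between sections with a possible bias, not as proof that baseline was contaminated. The Timeline allows baseline HbA1c to follow training in intervention SDHOs only, and the sections that date baseline to randomization cannot be satisfied when patients are recruited afterwards. If training lowers HbA1c before baseline, the primary estimate is pulled toward no effect by slope × b. This mechanism threatens power and the size of the estimate; it does not create a false positive.

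The documents do not fix the size. The fall from 0.5 to about 0.475 or 0.425 rests on full exposure, linear accrual, a slope of 0.6 and gaps of one or three months, all assumed. The loss would be small if patients were sampled soon after training, and absent if they were sampled before it.

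**What to change.** - **Timeline.** State that in each intervention SDHO the baseline laboratory samples are drawn before training, or before the decision-support function is activated. The app can still be used for case record capture, as Data Collection and Management requires. Control sites have no decision support but are covered by the same capture rule, which suggests that the two functions can be separated.
- **Month 0.** Define it once and use that definition in Primary Outcome, Secondary Outcomes, Timeline, and Data Collection and Management.
- **Patients already enrolled.** Report the training-to-baseline interval by cluster in the intervention arm. Add one prespecified sensitivity analysis of 12-month HbA1c that either uses, in both arms, the last HbA1c in SDHO records before randomization where one exists, or omits the post-training baseline covariate. Workflow Integration notes that "available laboratory records at SDHO are used for input into the platform", so records exist at the sites, but it does not say that they hold an earlier HbA1c for every patient.

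**Cost.** Some wording, one record extraction and one extra model. Earlier values will be missing for screen-detected and some other patients, possibly selectively, and some may be old. Omitting the covariate avoids that problem but loses precision. Both therefore belong in a sensitivity analysis beside the primary model, not in its place.

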### Eligibility Criteria

#### Inclusion Criteria

Aligning with the Thai public health screening policies, and in discussion with MOPH, patients attending SDHOs will be eligible to participate if they are (1) aged 30 to 70 years; (2) known cases of type 2 diabetes currently on oral hypoglycemic medications or identified to have diabetes in the initial screening by the community nurses; (3) have CKD-EPI eGFR of > 60 mL/min/1.73 m² [24]; and (4) undergoing treatment at the SDHOs by a community nurse.

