### Control Group

SDHOs randomized to the control group will continue with usual practice, without access to the training and support package, the CDSS and associated tools.

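### Patients are invited after allocation by nurses who evidently know their arm, and the primary model adjusts only for baseline HbA1c, so a difference between arms in newly identified patients could bias the primary estimate

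*Protocol article*

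**What the plan says.** All places are in the protocol article.

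- **Order of events (Timeline).** "SDHOs will be recruited and randomized before individual participant recruitment commences". Training of the intervention nurses comes after randomization, and the text then turns to enrolment: "Eligible patients with diabetes registered within the SDHOs will be invited by the community nurses to participate in this study".
- **Knowledge of arm (Intervention Group, Control Group).** Intervention nurses are trained, certified and given a tablet with the software. Control SDHOs carry on "without access to the training and support package, the CDSS and associated tools".
- **Eligibility (Inclusion Criteria).** Besides known cases on oral agents, the trial admits people "identified to have diabetes in the initial screening by the community nurses". Every participant must also be "undergoing treatment at the SDHOs by a community nurse".
- **Consent (Informed Consent).** Individual consent is "consent from patients with diabetes interested in participating in the study for data collection during the study".
- **Analysis (Statistical Considerations).** The primary analysis is a "linear mixed model including treatment arm and baseline HbA_1c_ as fixed effects", with SDHO as a random effect. Characteristics found to be unbalanced, at cluster or individual level, are added in a sensitivity analysis.

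**The concern.** Randomizing SDHOs balances, in expectation, the patients who belonged to them at that moment. It does not balance patients who are identified, invited and consented afterwards by staff who know the allocation. A trained intervention nurse and a control nurse may approach different patients, and different patients may agree.

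The eligibility rule gives one concrete route. Someone newly found to have diabetes and someone treated for years can have the same baseline HbA1c and still be expected to change differently over 12 months. Adjusting for baseline HbA1c removes imbalance in that variable only. Any remaining difference in case mix goes into the arm coefficient, which is the primary result of the trial.

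**Working it through.** **1. What the text fixes and what is inferred.** Stated: randomization precedes patient recruitment; community nurses invite; screening-detected cases are eligible; the primary model has arm, baseline HbA1c and SDHO. Inferred: nurses know their arm (from the nature of the intervention; blinding status is not stated); invitation follows training (from the order of the Timeline text). The timing of the initial screening relative to allocation is not given.

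**2. Form of the bias.** Let Δp be the difference between arms in the share of newly identified patients. Let g be the difference in 12-month HbA1c change between newly identified and known patients at equal baseline HbA1c. With no true effect, the arm coefficient is shifted by approximately

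bias = Δp × g.

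It is zero if either factor is zero, and its sign follows the signs of both. Neither factor is in the documents. Over an assumed grid of Δp from 0.05 to 0.30 and g from 0.3 to 1.0 points in absolute value:

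- smallest: 0.05 × 0.3 = 0.015 points, 3% of the 0.5-point target difference;
- middle: 0.10 × 1.0 = 0.10 points, 20% of the target;
- largest: 0.30 × 1.0 = 0.30 points, 60% of the target.

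**3. Standard error for the illustration.** The article gives no SD for HbA1c, so one must be assumed. As a guide, 770 per arm less 10% dropout (693), ICC 0.05, a difference of 0.5 and 90% power imply

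SD = 0.5 × √(693 / (2 × DE)) / (1.960 + 1.282).

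With 40 per cluster, DE = 1 + 39 × 0.05 = 2.95 and SD ≈ 1.67. With 1540/51 = 30.2 per cluster, DE = 2.46 and SD ≈ 1.83. I use 1.69 and show 1.5 and 1.83 beside it.

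Completers per cluster: 30.2 × 0.9 ≈ 27.2. DE = 1 + 26.2 × 0.05 = 2.31. Effective number per arm: 25.5 × 27.2 / 2.31 ≈ 300. SE = SD × √(2/300), which is 0.138 at SD 1.69.

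**4. Two-sided 5% error with no true effect.** Error = Φ(bias/SE − 1.96) + Φ(−bias/SE − 1.96).

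| Bias (points) | SD 1.5 (SE 0.122) | SD 1.69 (SE 0.138) | SD 1.83 (SE 0.149) |
|---|---|---|---|
| 0.015 | 5.2% | 5.1% | 5.1% |
| 0.05 | 6.9% | 6.5% | 6.3% |
| 0.10 | 12.9% | 11.2% | 10.3% |
| 0.20 | 37.2% | 30.5% | 26.8% |

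The SE ignores any precision gained from baseline adjustment. A smaller SE would make the error from a given bias larger.

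**The case against.** The strongest reply is that the route is narrow. Patients must be registered at the SDHO and under treatment there by a community nurse, so a screening-detected person must already have entered care. Screening looks routine in both arms: Health System in Thailand says each SDHO must report the percentage of its population screened, and Inclusion Criteria aligns eligibility with national screening policy. The section on algorithm development mentions screening, but the Intervention Group section does not describe a search for undiagnosed diabetes. The analysis section already allows for unbalanced characteristics. All of this stands, and it limits the risk without removing it: invitation and consent still follow allocation, and the sensitivity analysis depends on observed imbalance, covers measured factors only and leaves the headline estimate unchanged.

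A reader might infer more than the text supports:

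- *That nurses pick whom they like for a fixed number of places.* No quota or discretion is stated. The figure on randomization and sampling is not shown, so a sampling rule cannot be presumed absent.
- *That intervention nurses use the decision-support tool to find extra cases.* No passage says the initial screening uses the tool or follows allocation.
- *That the bias favours the intervention.* Trained nurses might equally invite patients who are harder to control.
- *That adding a known/new term is proven to cure the bias.* A simulation in which this is the only confounder must show that. It says nothing about unmeasured selection such as motivation.

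**Conclusion.** The concern holds as a risk, not as a demonstrated imbalance. The stated sequence allows recruitment to differ by arm, and the stated primary model corrects for one variable only. The effect could be negligible (0.015 points, error about 5%) or material (0.20 points, error about 31% at SD 1.69). Where it lies depends on two quantities the documents do not give, and the direction is open. The error rates rest further on the assumed SD, the stated ICC and dropout, and equal cluster sizes.

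This does not establish that the primary result will be invalid. It is a moderate point that deserves action because prespecified adjustment is an inexpensive improvement on the model as written.

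**What to change.** With 1599 patients enrolled by May 2024 (Results), recruitment can no longer be redesigned. Before the analysis:

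1. Add a fixed effect to the primary model for known and on oral agents versus newly identified at screening, derived from the medical history and current medication that the CRFs already collect (Data Collection and Management). Include it whether or not imbalance is observed.
2. Prespecify a sensitivity analysis restricted to previously known patients on oral agents and, where registration dates exist, to those registered before their SDHO was randomized. The article does not say that such dates are held.
3. Report the numbers eligible, invited and consented by arm and SDHO, where available.
4. Name recruitment after allocation as a limitation, because adjustment cannot remove unmeasured selection. The current limitations section does not mention it.

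The cost is analysis-plan wording, one derived variable and some tabulation. The restricted analysis is smaller and slightly less precise.
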